**Methods/design:**

The RSI@Work study is a randomised controlled trial that aims to assess the added value of a lifestyle physical activity intervention in addition to a work style intervention to reduce neck and upper limb symptoms in computer workers. Computer workers from seven Dutch companies with frequent or long-term neck and upper limb symptoms in the preceding six months and/or the last two weeks are randomised into three groups: (1) work style group, (2) work style and physical activity group, or (3) control group. The work style intervention consists of six group meetings in a six month period that take place at the workplace, during work time, and under the supervision of a specially trained counsellor. The goal of this intervention is to stimulate workplace adjustment and to improve body posture, the number and quality of breaks and coping behaviour with regard to high work demands. In the combined (work style and physical activity) intervention the additional goal is to increase moderate to heavy physical activity. The control group receives usual care. Primary outcome measures are degree of recovery, pain intensity, disability, number of days with neck and upper limb symptoms, and number of months without neck and upper limb symptoms. Outcome measures will be assessed at baseline and six and 12 months after randomisation. Cost-effectiveness of the group meetings will be assessed using an employer's perspective.

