### Rationale behind the study

The general model behind the present study is the dynamic model of workload presented by Van Dijk et al. [5]. According to this model, health effects may result from an imbalance between workload and capacity. By increasing capacity and decreasing workload this imbalance may be restored. The present study is designed to assess the effectiveness of an intervention that intends to decrease workload by improving work style and to increase capacity by improving general physical activity of computer workers with neck and upper limb symptoms. By comparing the effectiveness of a combined intervention (work style and physical activity) with a single intervention (work style) and a control intervention (usual care), the added value of a lifestyle physical activity intervention in addition to a work style intervention will be assessed. In addition, the effectiveness of a combined and single intervention will be compared with the effectiveness of usual care. Although general capacity is the result of physical as well as mental capacity, the RSI@Work study will primarily focus on the physical component.

In order to reduce workload, we will use a multidisciplinary approach to improve work style. The concept of work style was constructed by Feuerstein et al. [6] and represents the individual responses to high work demands. In the present study we defined work style as the following three individual responses to high work demands: 1. optimal body posture and proper workplace adjustment, 2. the number and quality of breaks and 3. coping with high work demands. The general idea is that, in case of high work demands, workers will be less inclined to pay attention to their body posture, adjust their workplace properly and use break and exercise reminder software.

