### Sample size and participant flow

The main primary outcome variable in this study is self-reported recovery. The intervention will be considered successful if recovery from work-related neck and upper limb symptoms (i.e. completely recovered or much recovered) is 20% higher in the intervention group than in the control group. The number of participants in each group needed to detect a difference in recovery of 20% between the intervention group and the control group was ± 80, with α = 0.05 (two sided) and β = 0.20. This number was based on our expectation that recovery would be 80% in the intervention group and 60% in the control group. However, since we expected a loss-to-follow-up of 40%, ± 135 workers were needed in each group at baseline. Based on our pilot study we expected that 6.25% of our source population would participate in the study, which brings the minimum number of workers that needed to be invited for participation at 6480 workers. Figure 1 shows that approximately 8000 workers were invited to participate and that 466 workers were randomised into the trial.

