### Data analysis

Intention-to-treat analyses will be used to estimate the effect of the intervention. Multilevel analyses will be used to investigate differences in recovery and changes in outcome variables between the intervention groups and the control group after six months and one year of follow-up. Multilevel analyses are used in order to adjust for possible dependency between observations from the same company.

Cost-effectiveness ratios will be calculated by dividing the difference between the mean costs by the difference in the mean effects in the primary outcome variables. Bootstrapping will be used to calculate the confidence intervals for the cost-effectiveness ratios. Ratios will be graphically presented on a cost-effectiveness plane. Furthermore, acceptability curves will be calculated for both interventions showing the probability of being cost-effective a specific ceiling ratio.

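### The main aim is the added value of physical activity over work style alone, but Data analysis names only comparisons with control and the sample size was set only for intervention versus control

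*Protocol article*

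**What the plan says.** **Aim.** In the abstract (Methods/design) the trial "aims to assess the added value of a lifestyle physical activity intervention in addition to a work style intervention". The Rationale says that, by comparing the combined intervention with work style alone and with usual care, "the added value of a lifestyle physical activity intervention in addition to a work style intervention will be assessed". The comparisons with usual care come second: "In addition, the effectiveness of a combined and single intervention will be compared with the effectiveness of usual care". The Discussion describes the same three-group comparison and closes by restating the added-value aim.

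**Sample size and participant flow.** "The main primary outcome variable in this study is self-reported recovery", counted as complete or much recovery. Success is a recovery proportion 20 points higher with intervention than with control. About 80 per group were "needed to detect a difference in recovery of 20% between the intervention group and the control group", "with α = 0.05 (two sided) and β = 0.20", on the expectation that "recovery would be 80% in the intervention group and 60% in the control group". Allowing for 40% loss, about 135 per group were wanted at baseline; 466 workers were randomised over three arms. No recovery rate is given separately for work style alone, and no difference is given between the two interventions.

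**Data analysis.** Multilevel analyses, by intention to treat, are to investigate "differences in recovery and changes in outcome variables between the intervention groups and the control group" at six months and one year. No sentence in that section names combined versus work style.

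**The concern.** The article states its aim, success criterion, sizing contrast and analysis contrast. The last three agree with one another and differ from the first. Carried out as worded, the analysis would report each intervention against control and would not estimate the difference between the two interventions, which is the question in the abstract.

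Two things are at stake. First, if the contrast is not fixed in advance, its model, covariates and time point can be chosen after the data are seen. Second, a reader will take the 80% power in the sample size section to apply to the main aim. It applies to a different comparison with a larger expected effect, so a non-significant added-value result could be misread as evidence that physical activity adds nothing. The last section of the Discussion says that the results should help occupational physicians decide whether to use a combined approach, and that decision depends on this contrast.

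**Working it through.** **Inputs from the article (Sample size and participant flow; Treatment allocation).** Recovery 80% vs 60%; two-sided α = 0.05; power 0.80; 40% loss; 466 randomised; blocks of three over three arms, so equal allocation.

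**Formulas.** Two independent proportions, normal approximation, with p̄ the mean of p1 and p2:

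- n per arm = [1.96·√(2p̄(1−p̄)) + 0.842·√(p1(1−p1) + p2(1−p2))]² / (p1−p2)²
- power = Φ{ [|p1−p2|·√n − 1.96·√(2p̄(1−p̄))] / √(p1(1−p1) + p2(1−p2)) }

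**Step 1: the plan's own figure.** For 80% vs 60%: [1.96·0.648 + 0.842·0.632]² / 0.04 = 81.2, so 82 per arm. The unpooled form gives (1.96 + 0.842)²·(0.16 + 0.24)/0.04 = 78.5, so 79. The stated ± 80 reproduces. Loss: 80/0.6 = 133.3, so 134, against ± 135 stated. Invitations: 3 × 135/0.0625 = 6480, exact. The arithmetic is sound for one intervention against control.

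**Step 2: numbers available per arm.** Planned evaluable: 80. With 466 randomised: 466/3 = 155.3 with no loss, and 155.3 × 0.6 = 93.2 with 40% loss.

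**Step 3: power for combined versus work style.** The article gives no rate for work style alone, so every pair in the first four rows is an assumption. Example, 90% vs 80% at n = 80: (0.10·8.944 − 1.96·0.505)/0.500 = −0.19, and Φ(−0.19) = 0.42.

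| Assumed recovery | n = 80 | n = 93 | n = 155 (no loss) |
|---|---|---|---|
| 90% vs 80% | 42% | 48% | 70% |
| 80% vs 75% | 11% | 13% | 18% |
| 80% vs 70% | 31% | 35% | 53% |
| 80% vs 65% | 57% | 63% | 84% |
| 80% vs 60% (the stated control comparison) | 79% | 85% | 97% |

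**Step 4: gain over work style detectable with 80% power.** Solve the power formula for p1 with p2 fixed at the assumed work style rate:

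| Assumed work style rate | n = 80 | n = 93 |
|---|---|---|
| 80% | 14.7 points | 13.8 points |
| 75% | 16.4 | 15.4 |
| 70% | 17.9 | 16.8 |
| 65% | 19.1 | 17.9 |
| 60% | 20.1 | 18.8 |

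A figure of about 15 points at 80 per arm therefore holds only if work style alone reaches 80%.

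**Step 5: numbers that smaller gains would need.** 80% vs 70% needs 294 evaluable per arm, and 90% vs 80% needs 199. Both exceed the 155 per arm randomised, even with no loss.

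**The case against.** The strongest reply is that the comparison is planned. The Rationale and the Discussion both say that the combined arm will be compared with work style alone, and a multilevel model with three randomised arms can yield that contrast. Comparison with usual care is itself a stated objective, so the control contrast is legitimate. A journal article may also leave the listing of contrasts to a fuller document. This stands to a point: it would be wrong to say that the added-value question goes untested. It does not remove the mismatch, because the article does state a contrast in its analysis section and another in its sizing, and neither is the one that answers its aim.

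Two stronger readings are tempting but unsupported:

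- **That added value would be judged by one intervention being significant against control and the other not.** This would be an invalid inference, but the article nowhere says that it will be made, nor that separate two-arm models will be fitted.
- **That 80% recovery was assumed in both intervention arms, so that the planned added value is zero.** The sample size section speaks of one intervention group in the singular and gives no rates by arm, so this is only one reading.

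It is also fair to say that the power figures rest on rates the article does not give. They concern only binary recovery, although other primary outcomes are listed. Recovery is, however, the outcome that the article itself calls the main one and uses for sizing.

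**Conclusion.** The point holds in this form: the contrast that answers the main aim is announced in the Rationale and Discussion, but it is not named in Data analysis, and the success criterion and sample size do not address it. The stated 80 per group is correct for 20 points versus control.

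For combined versus work style, 80% power exists only for gains of about 15 to 20 points at 80 per arm, or about 14 to 19 at 93 per arm, depending on the work style rate. A 10-point gain has 31% to 42% power at 80 per arm and stays below 80% even if all 466 are followed (53% to 70%). Large gains are covered: 95% vs 80% has 82% power at 80 per arm, and 80% vs 65% has 84% if nobody is lost.

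These figures assume equal arms, binary recovery, unadjusted two-sided α of 0.05, no clustering effect, and work style rates between 60% and 80%.

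**What to change.** **Data analysis.** Fit one three-arm multilevel model per outcome. Name combined minus work style as the contrast that answers the aim, reported as a difference with a 95% confidence interval. State each intervention versus control separately. Add that added value will not be inferred by comparing the two results against control.

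**Sample size and participant flow.** Say that about 80 evaluable per group gives 80% power only for the 20-point difference versus control. Give the detectable added-value difference as a range, each value tied to its assumed work style rate: at 80 per arm, about 15 points from 80%, 16 from 75%, 18 from 70%, 19 from 65% and 20 from 60%; at about 93 per arm, 14 to 19 points. A single unconditional figure should not be written in.

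**Cost.** Wording in two sections and one model contrast from data already being collected. Randomisation is complete, and no participants should be added. The downside is a less favourable precision statement for the main aim.

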### Treatment allocation

An independent statistician prepared the randomisation by using a computer-generated randomisation. To prevent unequal randomisation, workers were pre-stratified by company and baseline sports participation assessed with the baseline questionnaire. Furthermore, block randomisation with blocks of three was used. The researchers prepared the envelopes containing the allocation to the intervention group and made two boxes with envelopes for each company. The first box contained the envelopes for workers who participated in sports activities (i.e. at least twice a week during at least 20 minutes at a moderate intensity level). The second box contained the envelopes for workers who did not participate in sports activities. Directly after the baseline measurements were completed the researchers opened the envelope and informed the worker about the group allocation. Workers who did not participate in the baseline measurements but sent their completed questionnaire and informed consent by post were randomised at the VU university medical center and informed about their treatment allocation by phone or by email.

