### Description of the intervention

Like previous lifestyle physical activity intervention studies [24], the RSI@Work intervention is based on theoretical models of behaviour change, i.e. the Trans Theoretical Model (TTM) and the Precaution Adoption Process Model (PAPM). The TTM separates behaviour change into five discrete stages that are defined by a person's past behaviour and his or her plans for future action [25]. The PAPM resembles the TTM stages but introduces two new stages. These new stages distinguish between people who are unaware of an issue (Stage 1) and those who know something about an issue but never actively thought about it (Stage 2) [26]. Concepts of the PAPM and TTM, such as stage of change, awareness, self-efficacy and decisional balance, are used in the group meetings and applied to both the work style and the combined (work style and physical activity) intervention.

The interventions for the two intervention groups both consist of six interactive group meetings in a six-month period. All group meetings take place at the workplace, during work time (with permission of the employee) and under the supervision of a specially trained counsellor. The counsellors use standardized protocols that have been tested and improved during the pilot study. Four out of six meetings are large group meetings with maximally 10 participants. Two out of six meetings are small group meetings with maximally four participants. The goal of all group meetings is behavioural change with regard to physical activity and/or work style. The goal of the large group meetings is to provide general information and to raise awareness about work style and/or physical activity, and to discuss and find solutions for general barriers with regard to behavioural change. The goal of the small group meetings is to provide participants with tailored advice based on their stage of change with regard to work style and/or physical activity. In addition, solutions for individual barriers with regard to behavioural change are discussed.

The counsellor provides the work style part to both intervention groups and the physical activity part to the 'work style and physical activity group' only. The group meetings of the 'work style and physical activity group' are separate from the group meetings of the 'work style group'.

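### The multilevel model adjusts for company, which was a randomisation stratum, but not for the meeting groups that exist only in the two intervention arms, so standard errors are understated, most for combined versus work style.

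*Protocol article*

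**What the plan says.** All places are in the protocol article.

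- **Data analysis.** Multilevel models will compare the arms at six and 12 months. One reason is given: "Multilevel analyses are used in order to adjust for possible dependency between observations from the same company". Neither meeting group nor any other level is named. Confidence intervals for the cost-effectiveness ratios come from bootstrapping, with no resampling unit given.
- **Treatment allocation.** Randomisation is by individual, in blocks of three, and "workers were pre-stratified by company and baseline sports participation".
- **Description of the intervention.** Both interventions are delivered in interactive group sessions: "Four out of six meetings are large group meetings with maximally 10 participants". The other two meetings have at most four. The two arms meet separately.
- **Blinding; Group meeting 6.** Controls attend no meetings.
- **Group meetings 2, 3 and 5; Discussion.** Group members look for solutions to barriers together, assess one another's workplaces, and those further along in behaviour change are asked to support the others.
- **Sample size and participant flow.** The calculation has no term for clustering.

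**The concern.** Company is crossed with arm: each company supplies workers to all three arms in near-equal numbers. A company effect therefore enters both sides of an arm contrast and largely subtracts out. A company intercept is proper, but it deals with a nuisance that stratified randomisation has already mostly removed.

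The meeting groups are different. They form after randomisation, and each sits inside one arm. Mutual influence within the group is an intended mechanism of the intervention. A group that goes well or badly shifts all its members together, and no matching group in the other arm offsets the shift. A company term cannot absorb this. The design is partially nested: the two active arms are grouped and the control arm is not.

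At stake is the validity of the intervals and tests. The effect is greatest for combined versus work style, because both of those arms are grouped. That contrast is the added-value question the trial was built to answer.

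**Working it through.** **Inputs from the article.** Error rates: "with α = 0.05 (two sided) and β = 0.20". Rates: "recovery would be 80% in the intervention group and 60% in the control group". Number per arm: "between the intervention group and the control group was ± 80". Loss: "we expected a loss-to-follow-up of 40%, ± 135 workers were needed in each group at baseline". Recruitment: "466 workers were randomised into the trial". Group ceiling: 10. Equal allocation is inferred from blocks of three for three arms.

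**Assumptions.** The meeting-group ICC is not given; 0.01 to 0.10 is shown. Analysed group size is m = 6, from 10 × 0.6 after 40% loss. m = 10 is shown as the ceiling (full groups, no loss).

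**The plan's own figures.** Pooled two-proportion formula: [1.96√(2 × 0.7 × 0.3) + 0.84√(0.8 × 0.2 + 0.6 × 0.4)]² / 0.2², rounded up, gives 82 per arm. The unpooled formula gives 78.5 and the arcsine formula 80.3. Then 80/0.6 = 133.3, so 134, against the stated 135; and 3 × 135/0.0625 = 6480. The plan reproduces, with independent observations.

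**Effect of omitting meeting group.**
- Design effect: DE = 1 + (m − 1) × ICC.
- True over reported standard error: √DE when both arms are grouped; √((DE + 1)/2) when one is.
- Actual two-sided type I error: 2[1 − Φ(1.96/ratio)].

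Example, m = 6 and ICC 0.05: DE = 1 + 5 × 0.05 = 1.25. Combined versus work style: √1.25 = 1.118, 1.96/1.118 = 1.753, error 8.0%. Versus control: √1.125 = 1.061, 1.96/1.061 = 1.848, error 6.5%.

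| m | ICC | DE | Combined vs work style | Intervention vs control |
|---|---|---|---|---|
| 6 | 0.01 | 1.05 | 5.6% | 5.3% |
| 6 | 0.02 | 1.10 | 6.2% | 5.6% |
| 6 | 0.05 | 1.25 | 8.0% | 6.5% |
| 6 | 0.10 | 1.50 | 11.0% | 8.0% |
| 10 | 0.01 | 1.09 | 6.1% | 5.5% |
| 10 | 0.02 | 1.18 | 7.1% | 6.1% |
| 10 | 0.05 | 1.45 | 10.4% | 7.7% |
| 10 | 0.10 | 1.90 | 15.5% | 10.4% |

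**Simulation under no treatment effect.** Seven companies, 22 or 23 workers per company and arm, meeting groups of at most 10 nested in company and arm, a normal outcome, company intercepts fitted, meeting group omitted, 4000 runs per setting (Monte Carlo standard error near 7%: √(0.07 × 0.93/4000) = 0.4 points).

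| ICC | Retained | Combined vs work style | Work style vs control |
|---|---|---|---|
| 0 | 100% | 4.9% | 4.8% |
| 0 | 60% | 4.9% | 5.2% |
| 0.05 | 100% | 8.7% | 7.2% |
| 0.05 | 60% | 7.4% | 7.1% |
| 0.10 | 100% | 13.1% | 8.9% |
| 0.10 | 60% | 10.1% | 7.5% |

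The error is about 5% at ICC 0, so the omitted level is the cause. The simulated groups hold 7 or 8 before loss (22 split into three), which explains values below the m = 10 rows.

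**Power at the number actually randomised.** 466/3 = 155.3 per arm; × 0.6 = 93.2 after loss. For 80% versus 60% at 93 per arm, with the design effect on the intervention arm only and m = 6, the pooled formula gives 83.5%, 81% and 77% at ICC 0.02, 0.05 and 0.10. The unpooled formula gives 85%, 83% and 79.5%. Without clustering the pooled figure is 85%.

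**The case against.** The strongest reply is that the size rests wholly on an assumed ICC. Outcomes are individual self-reports at six and 12 months, contact time is modest, and a low ICC cannot be excluded. At 0.01 the actual error is under 6% with 6 per group. This stands as a limit on size. It does not change the direction, which holds for any positive ICC.

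It may also be said that model detail belongs in an analysis plan that is not shown. That would answer silence on clustering. But the article does state which dependency the model is for, and it names the level that matters least for the arm contrasts.

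Several stronger readings are tempting but not supported:

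- **Lost power.** A reader might infer that the planned 80% power is not delivered. At the roughly 93 per arm expected from the number randomised, power with 6 analysed per group stays near or above 80% over most of the ICC range. Pairing 80 per arm, which is already net of loss, with full groups of 10 mixes incompatible inputs.
- **Counsellor as a further level.** The article describes the counsellor as giving the work style part to both active arms. A shared counsellor effect would therefore tend to cancel in combined versus work style, as company does.
- **Errors of 13% to 16%.** These need an ICC of 0.10 and no loss to follow-up; the top of that range also needs every group at its ceiling of 10.
- **Company wrongly included.** It was a stratum and belongs in the model. Whether it is fixed or random is a matter of preference.

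**Conclusion.** The point holds as a missing level in a stated model. Analysed as written, the trial would report standard errors that are too small whenever outcomes correlate within meeting groups. With about 6 analysed per group and an ICC of 0.01 to 0.10, the actual error of a nominal 5% test is about 5.5% to 11% for combined versus work style and 5% to 8% versus control. At ICC 0.05 the formula gives 8.0% and 6.5%, and the simulation with 60% retained gives 7.4% and 7.1%. The inflation is small at an ICC of 0.01 to 0.02 and material from about 0.05, chiefly for the added-value contrast.

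This rests on the assumed ICC range, groups near their ceiling before loss, and the 40% loss the article expected. Recruiting beyond the target does not remove it, because the error rate depends on group size and ICC and not on the number per arm.

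**What to change.** Before the effect analyses are run:

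1. Add a random effect for large meeting group in the two intervention arms only. Treat each control as a singleton and use small-sample degrees of freedom. Use the large group because the article does not say that the small groups are nested in it.
2. Keep company in the model, fixed or random, and add the baseline sports stratum.
3. Resample the cost-effectiveness bootstrap by meeting group in the intervention arms and by individual among controls.
4. Report the estimated meeting-group ICC with its interval.

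The change affects analysis only, not conduct. It costs slightly wider intervals and requires a record of who belonged to which group. The section on co-intervention and compliance says counsellors check presence at each meeting, so membership should be recoverable, but this is an inference and needs confirming. If the ICC proves close to zero, little is lost.

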#### Secondary outcome variables

1. Physical activity is assessed by means of the validated Short Questionnaire to Access health enhancing physical activity (SQUASH) [30]. The SQUASH questionnaire contains questions about activities in the following four domains: 1) commuting activities (i.e. walking and cycling), 2) activities at work and school, 3) household activities, and 4) leisure time activities (i.e. walking, cycling, gardening, chores, and sports).

2. Body posture and workplace ergonomics during computer work (self reported). Participants rate themselves on the tendency of forward chin movement relative to the trunk in the direction of the computer screen (yes/no), using a document holder (yes/no), location of documents while working with them (right or left from keyboard, behind keyboard, in front of keyboard), keyboard height compared to elbow height (keyboard above elbow height, keyboard at or below elbow height), the tendency to work with raised shoulders (yes/no), keyboard flat on the desk (yes/no), use of mouse (yes/no), left handed (yes/no), hand that controls the mouse (left/right/both), convenient body posture while working with the keyboard and the mouse (yes/no).

3. Body posture and workplace ergonomics during computer work (observed). The following aspects will be observed, using a checklist while the participant is working: position of the participant in relationship to the position of the computer screen (rotation < 10°, rotation ≥ 10°), rotation of keyboard compared to table edge (rotated < 10°, rotated ≥ 10°), rotation of the neck (rotated < 20°, rotated ≥ 20°), height of the computer screen (top of screen far beneath eye height, at eye height, above eye height), viewing distance (shortest distance between the eyes and the computer screen) using a measuring tape, posture of the back while seated (straight/not straight), back supported up to shoulder blades (yes/no), body posture more or less symmetrical (yes/no), support of the elbows while typing (yes/no), ulnar deviation of wrists while typing (yes = ≥ 20°, no = < 20°), lower arm continuously supported (at least 50%) while working with the mouse (yes/no), ulnar wrist deviation while working with the mouse (yes = ≥ 20° or < -5° ; no = < 20° and > -5°).

4. The use of breaks and exercise reminder software and the number of breaks will be assessed by questionnaire.

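### Allocation is stratified by company and baseline sports participation, but the analysis section names only company; if sports participation predicts the outcome, a little precision is lost.

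*Protocol article*

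**What the plan says.** Under Treatment allocation, the article reports that "workers were pre-stratified by company and baseline sports participation assessed with the baseline questionnaire", and that "block randomisation with blocks of three was used". Each company had a pair of envelope boxes, one for workers who took part in sports and one for those who did not. The dividing line was sport "at least twice a week during at least 20 minutes at a moderate intensity level".

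Under Data analysis, the plan is: "Multilevel analyses will be used to investigate differences in recovery and changes in outcome variables between the intervention groups and the control group". The reason given for the multilevel form is: "Multilevel analyses are used in order to adjust for possible dependency between observations from the same company". Sports participation is not mentioned there.

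Under Sample size and participant flow, the lead endpoint is named: "The main primary outcome variable in this study is self-reported recovery". The Measurements section adds that recovery is assessed only at the two follow-up visits, so it has no baseline value. Physical activity (a questionnaire that counts sports) and cardiorespiratory fitness are secondary outcomes.

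**The concern.** Stratified blocks balance the sports factor across the three arms, so its share of the outcome variance is largely removed from the arm contrast. A model without the factor leaves that share in the residual. The reported standard error then overstates the real sampling variation, the test rejects a true null less often than 5%, and some power is given up. The design has paid for this balance, and the stated analysis does not visibly use it. What is at stake is precision only: the treatment estimate stays unbiased and false positives do not increase.

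**Working it through.** **1. The plan's own figure.** Inputs from the sample size section: recovery 80% v 60%, two-sided α = 0.05, β = 0.20.
- Unpooled variance: (1.96 + 0.84)² × (0.16 + 0.24) / 0.20² = 78.5, so 79 per arm.
- Pooled variance: [1.96√(2 × 0.7 × 0.3) + 0.84√0.40]² / 0.20² = 81.2, so 82 per arm.
- The stated ± 80 lies between the two. 80 / 0.6 = 133.3, so 134 against the stated ± 135. 3 × 135 / 0.0625 = 6480, as stated.

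The sample size reproduces and does not depend on this point.

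**2. Recovery.** Take 80 analysed workers per arm, two equal strata and a recovery difference d between strata in every arm. The values of d and the equal split are assumptions; the article gives neither.
- Variance used when the stratum is omitted: 0.40 / 80, SE 0.0707.
- True variance under stratum balance: (0.40 − d²/2) / 80.
- Power omitted = Φ[(0.20 − 1.96 × 0.0707) / true SE]. Power included = Φ[0.20 / true SE − 1.96].

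| d | True SE | Reported / true SE | Power omitted | Power included |
|---|---|---|---|---|
| 10 points | 0.0703 | 1.006 | 80.9% | 81.2% |
| 20 points | 0.0689 | 1.026 | 81.4% | 82.7% |
| 30 points | 0.0666 | 1.061 | 82.2% | 85.1% |

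The gain is 0.3, 1.3 and 2.9 power points. The corresponding type I error, 2Φ(−1.96 × ratio), is roughly 4.9%, 4.4% and 3.8%.

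**3. Effect of loss to follow-up.** These ratios assume exact balance among analysed workers. The article expects 40% loss. If that loss is random, it restores part of the imbalance, and the true variance of the unadjusted contrast becomes about 1 − 0.6R² of the total instead of 1 − R², where R² is the share of outcome variance explained by the stratum. For recovery, 0.40 − d²/2 becomes 0.40 − 0.6 × d²/2. The ratios fall to 1.004, 1.015 and 1.036, and power omitted to 80.8%, 81.1% and 81.6%. The test is less conservative, but the case for adjusting remains, because the model would then correct the imbalance that the loss creates.

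**4. Outcomes analysed as changes.** A simulation used 7 companies × 2 strata, blocks of three, 462 workers, 40% random loss, company as fixed effects, baseline to follow-up correlation 0.5, a stable 1 SD difference between strata and an arm effect of 0.4 SD. All but the companies, strata, block size and loss rate are assumptions; 462 approximates the 466 randomised.

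| Response | Mean SE, omitted v included | Power, omitted v included |
|---|---|---|
| Follow-up value | 0.166 v 0.148 | 68% v 76% |
| Change from baseline | 0.148 v 0.148 | 77% v 77% |
| Follow-up adjusted for baseline | 0.1325 v 0.1284 | 85% v 87% |

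A stable stratum difference cancels in a change. It does not cancel if change itself differs by stratum, for example through regression to the mean around a baseline activity threshold. Suppose a median split on a measure that correlates r with baseline activity and relates to follow-up only through it, with baseline to follow-up correlation ρ. The stratum then explains R² = r²(1 − ρ)/π of the change variance:
- ρ = 0.7, r = 0.6: 0.36 × 0.3 / π = 3%.
- ρ = 0.5, r = 1: 0.5 / π = 16%.

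Under exact balance, standard errors are then 1/√(1 − R²) = 1.02 to 1.09 times too large, and power is 79% to 75% instead of 80%. Which case applies cannot be settled from the article.

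**The case against.** The strongest objection is that this argues from silence. The quoted sentence explains why multilevel models are used; it is not a list of covariates and does not exclude sports participation. The section on co-intervention and compliance foresees an adjustment for co-interventions that Data analysis never repeats, so the latter is not a full list of model terms. A condensed article may leave covariates to an analysis plan. This stands, and it is why the fix allows a one-line confirmation.

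The second objection is size. No figure in the article links sports participation to recovery, and recovery is itself rated against baseline, which may weaken any link. This also stands: with a stratum difference of up to 20 points the gain is about one power point. It does not remove the point for recovery, because that outcome has no baseline measurement from which a stratum difference could be subtracted.

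A reader might infer that the damage is greatest for physical activity and fitness, with the stratum explaining 20% to 30% of variance and intervals 12% to 20% too wide. The article does not support this. Such shares may suit the level of these outcomes, but the plan analyses changes. The 12% to 20% also assumes exact balance among analysed workers. With 40% random loss, 1/√(1 − 0.6R²) gives about 7% to 10% even for follow-up levels (a simulation of this gave 6% and 10%). These are also secondary outcomes; the added-value question concerns symptoms. Nor does the article say that the factor was chosen because it was expected to be prognostic: its stated purpose is to prevent unequal randomisation.

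**Conclusion.** The point holds as a minor, conditional one. The design uses two stratification factors and the analysis section names one. If the sports factor predicts the analysed response and is truly left out, inference is conservative and slightly less powerful, without bias. For the main primary outcome the loss is about 0.3 to 3 power points, resting on assumed stratum differences of 10 to 30 points, equal strata, 80 analysed per arm and near balance. For changes in physical activity and fitness it ranges from none, if the stratum difference is stable, to a modest loss if change differs by stratum. A certain or large loss for those outcomes cannot be derived from the article.

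**What to change.** Include the two-level sports stratum, as used to choose the envelope box, as a fixed effect beside company in the models for recovery and the other outcomes. If it is already included, say so in one sentence under Data analysis. For recovery, report the adjusted risk difference averaged over the strata. In a logistic multilevel model the added covariate changes the meaning of the odds ratio, and the averaged risk difference stays comparable with the 20-point planning difference.

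The cost is one parameter per model and one standardisation step for recovery. No new data are needed: sports status determined the box, so it is known for every randomised worker.
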